| **Dimension** | **Element/level** | **Outcomes** |
| --- | --- | --- |
| Reach | Describe target audience & proportion reached | Participation proportion for Primary outcome 1 - of proportion of eligible population completed risk assessment  Number excluded and reasons  Record contact type responded to (letter, phone, text, social) |
|  | Comparison of sample to the target population | Representativeness of risk assessment participants and non-participants (by age, gender and smoking history)  Representativeness of CT scan participants compared to those eligible for CT scan but did not consent to one/attend for scan |
| Effectiveness | CT scan uptake | Participation proportion for Primary outcome 2 - proportion of people eligible and who complete CT scan, by invitation arm  Number excluded and reasons |
|  | Quality of life  Participant experience | We will include a dimension based (Hua Oranga) (see Appendix 13)  Participant interview including anxiety and appropriateness of SDM, level of information, study materials and value of screen to participant and whānau |
| Adoption | Staff | Number and description of delivery agents (e.g. practice nurse, GP) per practice. Number and description of non-participants.  Number of staff attending standardised training session including an implementation manual and guide to the advanced form data entry system embedded in their Practice Management System (PMS). Pre and post training survey of knowledge and confidence, particularly in providing SDM. Survey include ability to feedback to improve future training (see Appendix 17)  For all above measures, timelines will also be monitored. |
|  | Setting | Proportion of primary care practices offered participation who choose to participate  Characteristics of participating and non-participating practices |
|  | System impacts | Audit against readiness assessment assumptions |
| Implementation | Setting | Number of claims & cost for completed screen events per practice  Triangulated with completion of the advanced form (checklist tool) for screen event – this tool will capture the key events for fidelity, time to complete the screen, text field for adaptations/issues/fixes to consider  Fidelity triangulated with research nurse observations of risk assessment completion  Ongoing partnership with providers and key stakeholders with iterative feedback including on barriers and adaptations made  Updating our cost effectiveness model with trial data |

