Appendix 17: Pre and post training evaluation form

### Appendix 1: Lung cancer screening study information booklet

###
[figure not shown]

###
[figure not shown]

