### Appendix 17: Training evaluation survey

Tēnā koe,

In your role as a provider of support to the participants of the Lung Screening Study, you recieved some training about the study, about lung cancer and about how to talk to participants with positive scans and concerning results. We would like to invite you to complete a short questionnaire to provide feedback on this training.

Your individual feedback will not be identifiable. Any report will only include summarised findings, meaning anyone reading the report will not be able to tell who took part in the survey or who said what,

Do I have to take part?

Your participation is voluntary- you do not have to participate if you don't want to. You can also decline to answer any specific questions. Whether or not you agree to take part will have no impact on your employment or on any other aspect of your work.

By answering these questions, you are consenting to the research team including this information in an analysis of how well the lung screening research programme is working. All answers are anonymous and you will not be able to be identified.

| **1)** | **Please indicate your role:** | ****  Practice Nurse  GP  Other  [reset](javascript:;) |
| --- | --- | --- |
| **2)** | Please rate your knowledge of the following **before** you received the study training:  **Lung cancer signs and symptoms** | \| \| 1- very poor \| 5 \| 9- very good \| \| --- \| --- \| --- \| \| \| \| \| --- \| --- \| --- \| --- \| --- \| --- \| \|  \|  \|  \| \| Change the slider above to set a response \| \| \|   [reset](javascript:;) |
| **3)** | **Appropriate referral pathways for people diagnosed with a lung nodule:** | \| \| 1- Very poor \| 5 \| 9- Very good \| \| --- \| --- \| --- \| \| \| \| \| --- \| --- \| --- \| --- \| --- \| --- \| \|  \|  \|  \| \| Change the slider above to set a response \| \| \|   [reset](javascript:;) |
| **4)** | **Before this study, how confident were you dealing with a person with a suspected lung cancer?** | ****No Confidence Uncertain Confident Very Confident  [reset](javascript:;) |
| **5)** | Please rate your knowledge of the following **after**you received the study training:  **Lung cancer signs and symptoms** | \| \| 1- very poor \| 5 \| 9- very good \| \| --- \| --- \| --- \| \| \| \| \| --- \| --- \| --- \| --- \| --- \| --- \| \|  \|  \|  \| \| Change the slider above to set a response \| \| \|   [reset](javascript:;) |

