| **6)** | **Appropriate referral pathways for people diagnosed with a lung nodule:** | \| \| 1- Very poor \| 5 \| 9- Very good \| \| --- \| --- \| --- \| \| \| \| \| --- \| --- \| --- \| --- \| --- \| --- \| \|  \|  \|  \| \| Change the slider above to set a response \| \| \|   [reset](javascript:;) |
| **7)** | **After this study, how confident are you dealing with a person with a suspected lung cancer?** | ****No Confidence Uncertain Confident Very Confident  [reset](javascript:;) |
| **8)** | **Please indicate how well you think the training prepared you to support participants of the Lung Screening Study:** | \| \| 1- Very poorly \| 5 \| 9- Very well \| \| --- \| --- \| --- \| \| \| \| \| --- \| --- \| --- \| --- \| --- \| --- \| \|  \|  \|  \| \| Change the slider above to set a response \| \| \|   [reset](javascript:;) |
| **9)** | **Specifically, please indicate how well you think the Shared Decision Making materials prepared you to support participants of the Lung Screening Study:** | \| \| 1- Very poorly \| 5 \| 9- Very well \| \| --- \| --- \| --- \| \| \| \| \| --- \| --- \| --- \| --- \| --- \| --- \| \|  \|  \|  \| \| Change the slider above to set a response \| \| \|   [reset](javascript:;) |
| **10)** | **Please indicate how helpful you found the Shared Decision Making process when explaining the study to potential participants:** | ****Not at all helpful Somewhat helpful Extremely helpful  [reset](javascript:;) |
| **11)** | **Do you have any comments that you would like to make about the training received?** | **** |

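### Table 3 names a pre- and post-training survey focused on shared decision making, but Appendix 17 is one post-training form with recalled baselines and no before/after item on shared decision making

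*Protocol*

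**What the plan says.** Under Secondary research questions, Table 3 of the protocol sets out the implementation outcomes by RE-AIM dimension. The Staff element of the Adoption dimension includes a "Pre and post training survey of knowledge and confidence, particularly in providing SDM". The next sentence names the instrument and a further purpose: "Survey include ability to feedback to improve future training (see Appendix 17".

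The list of appendices describes the same document as "Appendix 17: Pre and post training evaluation form". The appendix itself is headed as a training evaluation survey. Its opening text addresses people whose training is over: "you recieved some training about the study, about lung cancer and about how to talk to participants with positive scans and concerning results".

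The form asks for knowledge ratings before and after the training. For confidence it asks "Before this study, how confident were you dealing with a person with a suspected lung cancer" and later "After this study, how confident are you dealing with a person with a suspected lung cancer". On SDM it asks how well the materials prepared the respondent and, separately, "Please indicate how helpful you found the Shared Decision Making process when explaining the study to potential participants". It promises that answers are anonymous.

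**The concern.** Table 3 singles out one construct, staff knowledge of and confidence in providing SDM, and says it will be surveyed before and after training. The cited instrument is given only after training and contains no before/after question on that construct. A plan that names an outcome but supplies a form that does not collect it will leave a gap at reporting, and an analysis plan cannot recover a question that was never asked.

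Two further features weaken what the form does collect. The before ratings are recalled at the same sitting as the after ratings, so they are open to recall error and to a shift in how respondents judge their past selves. And the confidence questions are dated to the study, so the difference mixes any effect of training with experience gained by running the trial.

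At stake is one implementation measure in a trial that adopts an effectiveness-implementation hybrid design and makes implementation factors an objective. SDM is the step that leads to consent for the scan, so whether staff felt more able to deliver it is a reasonable thing to want to know. The loss is permanent for each person trained before the form is changed.

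**Working it through.** The plan states no figure for this survey, so the check compares each item of Appendix 17 with the outcome in Table 3 on three questions: when it is asked, what it measures, and whether both a before and an after rating exist.

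| Items | Subject | Before and after? | Anchor | On SDM? |
|---|---|---|---|---|
| 1 | Respondent's role | No | none | No |
| 2 and 5 | Knowledge of lung cancer signs and symptoms | Yes, before recalled | training | No |
| 3 and 6 | Knowledge of nodule referral pathways | Yes, before recalled | training | No |
| 4 and 7 | Confidence with a person with suspected lung cancer | Yes, before recalled | study | No |
| 8 | How well the training prepared the respondent | Once | after | No |
| 9 | How well the SDM materials prepared the respondent | Once | after | Materials only |
| 10 | How helpful the SDM process was | Once | after contact with potential participants | Process only |
| 11 | Free comments on the training | Once | after | No |

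1. Item count: 1 (role) + 6 (three pairs) + 1 (item 8) + 2 (items 9 and 10) + 1 (comments) = 11, all on one form.
2. Before/after pairs: 3, of which 2 are knowledge and 1 is confidence. Pairs with a rating taken before training: 0 of 3.
3. Pairs on SDM: 0 of 3. Items at any time on knowledge of, or confidence in, providing SDM: 0 of 11. Items 9 and 10 rate the materials and the process.
4. Anchors: items 2 and 5 name the training. Items 3 and 6, on "Appropriate referral pathways for people diagnosed with a lung nodule", follow directly from them and carry the same stem. Items 4 and 7 name the study. So 1 of the 3 pairs, the only one on confidence, covers a longer period than the training.
5. Could another form supply the missing data? The protocol does contain a slip in appendix numbers: the COPD qualitative section cites Appendix 17 for its interview guide, which appears as Appendix 15. But the list of appendices names no second training survey, so a wrong number in Table 3 would not explain the gap. Provider interviews and focus groups follow implementation and give no pre-training rating.

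Result: a recalled change is computable for three non-SDM subjects. No SDM change is computable.

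**The case against.** A good deal can be said for the form. Rating before and after on one sheet is a recognised design. It pairs each person's answers without an identifier, which fits the promise of anonymity. A prospective pair of forms would also be completed by people who know that training is being evaluated, so that source of bias would remain. Items 8, 9 and 11 serve the stated aim of improving future training. SDM is covered elsewhere, through provider interviews and focus groups and through participant surveys on the decision discussion. Staff knowledge and confidence do not appear among the listed secondary outcomes, and no estimate or test of a training effect is planned. All of this stands. It bears on how serious the mismatch is and does not remove it: Table 3 describes a survey that Appendix 17 does not deliver for SDM.

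Stronger readings are tempting, and the documents do not support them:

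- A reader might infer that the effect of training cannot be measured at all. Items 2 to 7 do give a self-reported change on three subjects. A recalled baseline is a weaker measure, not an absent one.
- A reader might infer that there are no data on staff readiness for SDM. Item 9 is a post-training rating of preparedness from the SDM materials, and item 8 one of preparedness overall.
- A reader might infer that the recalled ratings must show a false gain. That is possible, but the documents give no figure for the size of any such bias.
- A reader might infer that this change score feeds a national programme. Informing such a programme is a general aim of the study; nothing makes this score an input to it.

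**Conclusion.** The mismatch is real and minor. Followed as written, the plan cannot produce the change in SDM knowledge or confidence that Table 3 names: none of the three before/after pairs concerns SDM, and none of the 11 items asks about knowledge of or confidence in providing it. The three changes that can be computed are retrospective self-report, and the confidence change also reflects experience of running the trial.

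This rests on two assumptions: that Appendix 17 as shown is the whole instrument, and that no pre-training form exists outside the list of appendices. The measure is a descriptive Adoption line, so randomisation, sample size, the primary comparison and the listed secondary outcomes are unaffected.

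**What to change.** Preferred change:

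- Write identical items on knowledge of SDM and on confidence in providing it.
- Put them with items 2 to 4, reworded as current ratings, on a short form at the start of the training session, and repeat the same form at the end. Current ratings at two times need no before or after wording, which also removes the anchoring problem.
- Link the two forms by a code that respondents generate themselves, so answers stay anonymous. The present form has no linking field.
- Keep items 8 to 11 as later feedback.
- Report staff already trained separately, labelled as retrospective.

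Minimum change: add one before/after SDM pair to the existing form, anchor items 4 and 7 to the training, and reword Table 3 so that it describes a retrospective post-training evaluation.

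The cost is a few minutes per training session and a revised appendix. Staff trained before the revision cannot supply a true baseline, so the change is best made before further sessions are held.

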### Smoking cessation advice

All participants who are current smokers will be provided with brief advice to quit, offered nicotine replacement or other pharmacological treatments to support smoking cessation, and offered referral to quit services. For participants whose calculated risk means they are not eligible for lung cancer screening this will be provided at the completion of the risk assessment process. Participants who are eligible for screening but choose not to proceed with a CT scan will receive this (brief advice to quit, offers of medications and referral to cessation services) at that decision point. Participants who proceed to screening will be offered this when they are given their results. All relevant staff will receive training in smoking cessation support, and DHB and PHO smokefree services are aware of the project and are supportive.

## Statistical Consideration and Data Analysis

### Sample size and statistical analysis

The sample size for the overall randomised trial is calculated based on the power required to test the hypothesised difference in the number of participants completing lung cancer screening following an invitation to the study. Our sample size will provide more than sufficient power to test the hypothesised difference in completion of risk assessment. Sample size was calculated using the formula cited in Hade et al^51^. Table 4 outlines the assumptions made in the sample size calculation.

Table 4: Assumptions used in power calculation (MAIN STUDY)

| **Parameter** | **Assumed value** | **Justification** |
| --- | --- | --- |
| Proportion of Māori aged 55-74 who meet eligibility criteria to be invited for screening | 24% | Smoking history data collected in our pilot of AAA screening (28%), reduced by 4% to allow for those excluded on other grounds (terminal illness etc.). |
| Intraclass correlation coefficient | 0.03 | Approximately the median value of those cited in Hade et al. |
| Average number of eligible patients per practice | 24 | From practice population registers. Practices with <10 expected eligible patients will be excluded. |
| Proportion of Māori in eligible age range recorded as not “never smokers” | 70% | Data from one of the Auckland PHOs. |
| Proportion of not never-smokers eligible who complete risk assessment in the primary care group | 80% | It is difficult to estimate this parameter as there is no similar experience to base it on. However it would seem reasonable that it is possible to obtain smoking history on 70% of the eligible practice population in the control group, and that this could be 10% higher in the intervention group where primary care may have a significant advantage. |
| Proportion of not never-smokers eligible who complete risk assessment in central hub group | 70% |  |
| Screening uptake in the central hub group | 40% | Based on uptake rates routinely achieved for Māori in other screening programmes including bowel screening. |
| Screening uptake rate in primary care group | 50% | A goal of 10% higher uptake rate than the control group is both achievable and clinically meaningful |
| Variance reduction from regression adjustment of individual-level outcomes. | 10% | Consistent with variance reduction assumptions used by Hade et al. |
| Variance reduction from regression adjustment of group-level outcomes. | 20% | Consistent with variance reduction assumptions used by Hade et al. |
| Statistical power to detect 10% increase in screening uptake | 80% | Standard statistical power selection |
| Acceptable Type I error rate | 5% | Standard statistical significance selection |

Due to a lack of pilot studies from which to estimate the statistical power of the plasma biomarker analyses to be used here, plasma biomarkers were not included in these sample size calculations. This study will provide pilot data to inform power calculations for future studies.

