| Expected sample size | Our sample size estimate anticipates that 4412 participants will be invited to undergo risk assessment, with 3309 participants being expected to complete this assessment. Of these, we expect that 1134 participants will be eligible for low dose CT scanning, and that 500-550 participants will consent to undergo LDCT scan for lung cancer screening. After the first 50 participants have been scanned, we will pause the study assess the pathway and methods, to ensure they are optimal before expanding the study to the next 500 scans which will test the invitation methods. Should the proportions of participants agreeing to risk assessment and / or scan differ from our predictions, these numbers will be adjusted accordingly to allow us to reach the 500-550 scan target.  **COPD assessment:**  We conservatively estimate that 400 (80%) of our LCS participants will consent to COPD assessment. Of these, we assume at least 200 (50%) will meet the criteria for a COPD diagnosis, for whom we can assess changes in baseline management after sending the report to the GP. With a sample of 200 the study has 85% power to detect that a measured improvement in management is significantly greater than 10% when the actual proportion is 17% or more (95% significance level). |
| Recruitment | Letter or email sent to potentially eligible participants in both trial arms, with phone or text follow up.  Opportunistic recruitment in primary care arm if people attend the practice for another reason.  All participants will be assessed for their risk of lung cancer and those who proceed to a CT scan will also be invited to take part in a COPD assessment. |

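### Table 4's 80% power holds only among risk-assessed, scan-eligible people; for screening counted from invitation, the same inputs give about 66–68%

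*Protocol*

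**What the plan says.** The opening paragraph of Sample size and statistical analysis bases the size on the "difference in the number of participants completing lung cancer screening following an invitation to the study". Other sections take the same view. The Synopsis and Study Design describe pathways tested from invitation through to CT scan. The Primary outcome paragraph under Full trial asks whether a primary care invitation produces higher participation than a hub invitation.

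Table 4 supplies these planning rates:

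- Central hub uptake of 40%, with the reason "Based on uptake rates routinely achieved for Māori in other screening programmes including bowel screening".
- Primary care uptake of 50%, with the reason "A goal of 10% higher uptake rate than the control group is both achievable and clinically meaningful".
- Completion of risk assessment, listed separately: "Proportion of not never-smokers eligible who complete risk assessment in the primary care group | 80"% and "Proportion of not never-smokers eligible who complete risk assessment in central hub group | 70"%.

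Neither uptake row says what uptake is a proportion of. Two other places do bear on it. The Synopsis expects "1134 participants will be eligible for low dose CT scanning, and that 500-550 participants will consent to undergo LDCT scan". Table 3 describes a second primary outcome as CT completion among eligible people, by arm, and a first primary outcome as completion of risk assessment. The Primary outcome entry under Outcomes and Significance gives no denominator.

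**The concern.** The stated question and the powered contrast start at different points in the pathway. The question starts at invitation, where practices are randomised and everyone on the list can be counted. The powered contrast starts after risk assessment, in a group that Table 4 itself expects to form at different rates in the two arms.

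This matters in two ways. A reader who takes the sizing sentence at face value will believe the trial has 80% power for screening completed per person invited, and the protocol does not show that. An analysis confined to assessed and eligible people also compares groups selected after randomisation, and leaves out any benefit of primary care in getting people to risk assessment. The protocol should say which comparison the 80% belongs to.

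**Working it through.** **Inputs.** From Table 4: uptake 40% v 50%; risk assessment completed 70% v 80%; scan-eligible 24% and recorded as not never-smokers 70% of Māori in the age range; ICC 0.03; variance reduction 10% (individual) and 20% (group); type I error 5%. From the Synopsis: 4412 invited, 3309 assessed, 1134 eligible, 500–550 scans. From Study setting/Location: 48 practices, 24 per arm. Sidedness is not stated; a two-sided 5% level reproduces the sample size and a one-sided level does not (about 880).

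**Step 1: where 40%/50% is applied.**

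- 4412 × 0.75 = 3309 assessed, 0.75 being the average of 70% and 80%.
- 3309 × 24/70 = 1134 scan-eligible.
- 1134 × 0.45 = 510 scans, within the forecast of 500–550.

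The uptake rates are therefore applied after risk assessment and eligibility.

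**Step 2: reproduce the stated power.** With m people per practice, the variance factor is (1 − ICC) × 0.90 + m × ICC × 0.80.

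- m = 1134/48 = 23.6: factor = 0.873 + 0.567 = 1.44.
- Variance of the difference = (0.40 × 0.60 + 0.50 × 0.50) × 1.44 / 567 = 0.001244; standard error 0.0353.
- 0.10 / 0.0353 = 2.83. Power is 81% (normal) or 79% (t, 46 df).
- Solved for size with m = 24, the formula gives 1115 to 1126 people, against 1134.

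The calculation is sound for this contrast. The 70%/80% rows affect it only through the average of 75% that leads to 1134.

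**Step 3: the effect implied from invitation.**

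- Scan-eligible invitees: 0.70 × 0.40 = 28% v 0.80 × 0.50 = 40%, a gap of 12 points.
- All invited, multiplying by 24/70: 9.6% v 13.7%, a gap of 4.1 points.

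**Step 4: power over all invited.** Scan eligibility is unknown in anyone not assessed, so the fully observed denominator is everyone invited.

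- m = 4412/48 = 91.9: factor = 0.873 + 91.9 × 0.03 × 0.80 = 3.08.
- Variance = (0.096 × 0.904 + 0.137 × 0.863) × 3.08 / 2206 = 0.000286; standard error 0.0169.
- 0.0411 / 0.0169 = 2.43. Power is 68% (normal) or 66% (t, 46 df).

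**Step 5: sensitivity to the ICC.** Table 4 gives one ICC and does not say which outcome it describes. The two lower values are assumptions.

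| ICC | Power over all 4412 (t to normal) |
|---|---|
| 0.03 (Table 4) | 66–68% |
| 0.02 (assumed) | 78–79% |
| 0.01 (assumed) | 91–92% |

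**The case against.** The strongest reply is that nothing has been miscalculated. The forecast closes, the 80% reproduces, and Table 3 names CT completion among eligible people as a primary outcome, which is the contrast that was powered. Table 4's first row speaks of people meeting criteria to be invited for screening, and there the 24% is the scan-eligible group, so uptake per person invited for screening could mean uptake among that group. The phrase about following an invitation could describe sequence only. The Synopsis also allows numbers to be adjusted to reach the scan target.

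Most of this stands. It shows that the conditional reading is coherent and probably what was intended. It does not remove the mismatch. The sizing sentence speaks of an invitation to the study, and people are invited to the study before risk assessment. The end-to-end description of the design points the same way. Adjusting numbers to reach a scan total does not say which denominator is compared.

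Two stronger readings are tempting and the documents do not support them. A reader might infer that the primary care advantage is counted twice in the power. It is not: the 70% v 80% difference does not enter the 40% v 50% contrast, and the protocol treats risk assessment as an outcome in its own right. A reader might also infer that 40% must mean uptake per person invited, because it is borrowed from other programmes, so that the true contrast after assessment is much smaller than 10 points and the scan forecast is wrong. The protocol gives no denominator for those programme rates, and the 10 points are presented as a goal. The forecast of 500–550 scans agrees with the conditional reading and needs no change.

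**Conclusion.** The point holds as a mismatch of denominators, not as an arithmetic error. The 80% power is right for 40% v 50% among the 1134 people assessed and found eligible (79–81% recomputed). It is not the power for screening completed after invitation to the study, which the text says was the basis for the size. Under Table 4's own rates, that quantity is 9.6% v 13.7% of 4412 invited, with about 66–68% power.

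The lower figure assumes 48 practices of equal size, a two-sided 5% test, the plan's variance reductions, and an ICC of 0.03 applied to an outcome counted over all invited. The ICC matters most: at an assumed 0.02 the shortfall nearly disappears, and at an assumed 0.01 power exceeds 80%. The mismatch in wording does not depend on the ICC.

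**What to change.** 1. In Table 4, state that 40% and 50% are uptake among people who have completed risk assessment and been found scan-eligible, and that the 80% power applies only to that contrast.
2. Reconcile the opening paragraph of Sample size and statistical analysis, the Primary outcome paragraph under Full trial, and the two primary outcomes in Table 3, so that the primary outcome has one stated denominator.
3. Beside the conditional figure, report the implied invitation-level effect (28% v 40% of scan-eligible invitees; 9.6% v 13.7% of all invited) and its power of about 66–68% at ICC 0.03, saying which outcome the ICC is taken to describe.

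The 1134 and the 500–550 scan forecast stay as they are. The cost is text only, with no extra participants or practices. The drawback is that the stated power for the end-to-end question becomes less favourable than the 80% a reader would now assume.
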